# Adapting and implementing breast cancer follow-up in primary care: protocol for a mixed methods hybrid type 1 effectiveness-implementation cluster randomized study

**DOI:** 10.1186/s12875-023-02186-3

**Published:** 2023-11-09

**Keywords:** Cancer survivorship, Primary care, Breast cancer, EPIS, Practice change model, Implementation strategies

## Abstract

**Background:**

Advances in detection and treatment for breast cancer have led to an increase in the number of individuals managing significant late and long-term treatment effects. Primary care has a role in caring for patients with a history of cancer, yet there is little guidance on how to effectively implement survivorship care evidence into primary care delivery.

**Methods:**

This protocol describes a multi-phase, mixed methods, stakeholder-driven research process that prioritizes actionable, evidence-based primary care improvements to enhance breast cancer survivorship care by integrating implementation and primary care transformation frameworks: the Exploration, Preparation, Implementation, and Sustainment (EPIS) framework and the Practice Change Model (PCM). Informed by depth interviews and a four round Delphi panel with diverse stakeholders from primary care and oncology, we will implement and evaluate an iterative clinical intervention in a hybrid type 1 effectiveness-implementation cluster randomized design in twenty-six primary care practices. Multi-component implementation strategies will include facilitation, audit and feedback, and learning collaboratives. Ongoing data collection and analysis will be performed to optimize adoption of the intervention. The primary clinical outcome to test effectiveness is comprehensive breast cancer follow-up care. Implementation will be assessed using mixed methods to explore how organizational and contextual variables affect adoption, implementation, and early sustainability for provision of follow-up care, symptom, and risk management activities at six- and 12-months post implementation.

**Discussion:**

Study findings are poised to inform development of scalable, high impact intervention processes to enhance long-term follow-up care for patients with a history of breast cancer in primary care. If successful, next steps would include working with a national primary care practice-based research network to implement a national dissemination study. Actionable activities and processes identified could also be applied to development of organizational and care delivery interventions for follow-up care for other cancer sites.

**Trial registration:**

Registered with ClinicalTrials.gov on June 2, 2022: NCT05400941.

**Supplementary Information:**

The online version contains supplementary material available at 10.1186/s12875-023-02186-3.

## Background

Individuals living with a history of breast cancer are increasing in numbers and managing significant late- and long-term treatment effects and related symptom burden. Breast cancer is the most common cancer, excluding non-melanoma skin cancers, for women in the U.S. [1]. There are more than 3.5 million individuals with a history of invasive breast cancers in the United States (U.S.), with more than 2.6 million (75%) being 60 years of age or older [1]. Driven by innovations in early detection and adjuvant treatment, relative survival rates for breast cancer has continually improved [2], at 5-years (89%), 10-years (83%), and 15-years (78%) post-diagnosis resulting in surges in people living long-term after a breast cancer diagnosis [1]. Most of these individuals are diagnosed with localized breast cancers (61%), which have a relatively high survival rate (99%) [1]. Nevertheless, there are significant adverse late and long-term post-treatment effects. Adverse health outcomes post-treatment for breast cancer may include lymphedema [3], chronic pain [4–6], anxiety and depression [7, 8], sarcopenic obesity [9], bone loss and fracture risk [10, 11], declines in cognitive function [12–14], stroke [15], cardiovascular disease [16, 17], sexual dysfunction [18, 19], neuropathy [20, 21], and fatigue [22].

From 2012 to 2025, the overall market demand for oncology is projected to rise by 40% resulting in shortages of oncologists to meet both follow-up care and increasing treatment demand [23–25]. Adult cancer survivors acknowledge preferring follow-up care driven by cancer specialists rather than primary care [26]. Yet, the percentage of people with a cancer diagnosis visiting cancer and cancer-related physicians declines each year, and recent estimates suggest that their care continues in primary care settings [27]. Nearly 75% of women who had a history of breast cancer saw primary care clinicians, and these percentages did not decrease annually [28]. Serious challenges remain in transferring actionable information from cancer care to primary care, which is a significant problem for breast cancer populations who require long-term surveillance [26].

### Survivorship and primary care

There is unrealized potential for primary care to have a greater role in the care of patients with a history of breast cancer [29]. In two Canadian randomized controlled trials (RCTs), primary care clinicians were as effective at detecting recurrence in breast cancer survivors as hospital-based systems, with greater patient satisfaction [30] and no differences in psychosocial outcomes [31]. People with a history of breast cancer rate primary care clinicians higher for coordination of care and comprehensive care than oncologists for services that include tracking of care, ongoing management of medical problems and preventive care [32, 33]. However, the U.S. system is plagued with fragmentation between specialty and primary care prompting the American College of Surgeons’ Commission on Cancer (CoC) to initially mandate [34, 35] the implementation of survivorship care plans (SCP) as a communication tool [36, 37]. Yet, primary care guidelines and survivorship care plans have not produced the necessary changes for better care because they often do not address implementation challenges in the broader primary care context.

While SCPs have been shown to increase the likelihood that primary care clinicians report engaging in survivorship care planning [38], primary care practice innovators have voiced frustrations about the investments to support SCP development [36, 37] despite limited effectiveness in patient-reported outcomes [39, 40]. A third of patients with a history of cancer believe there is a shared care role for primary care in cancer follow-up, suggesting opportunities to perform routine cancer-screening tests, supplement cancer and cancer-related specialist care, and provide follow-up medical care when “enough time has passed” [26]. Yet, ‘shared care’ for patients with a history of breast cancer, where multiple teams (primary care, oncology, and medical subspecialists) jointly participate in care delivery, remains consistently understudied [41]. Studies investigating implementation activities to enhance primary care capacity to participate in shared care models are urgently needed [42, 43].

Cancer care delivery research is an emerging dissemination and implementation science research area and research priority for National Cancer Institute (NCI) [44]; however, many efforts to date have been insufficiently informed by implementation science theories and methods [45]. Most U.S. cancer survivorship studies focus on implementation of cancer survivorship care plans in oncology. Few address important context and process factors affecting their use in primary care or post-cancer treatment settings [40, 46, 47]. Few U.S. based studies explore implementation of evidence-based interventions (EBIs) for patients with a history of cancer [44], and similarly few studies address implementation of EBIs or scaling up in primary care settings [48]. A recent review of SCPs notes “survivorship care models in real-world settings will likely require moving beyond traditional randomized controlled trials to conduct research informed by implementation science methodology” [40]. Our study addresses these issues using a “designing for dissemination” perspective [49–51] while attending to important context, capacity and patient complexity factors impacting the implementation of breast cancer follow-up care in primary care.

### Conceptual frameworks

The design of this study integrates the Exploration, Preparation, Implementation, and Sustainment (EPIS) framework and the Practice Change Model (PCM). EPIS is a program implementation-based framework that provides assessment constructs for exploring inner and outer context factors that impact evidence-based intervention implementation [52–54]. Exploration is the act of evaluating whether the intervention fits the current environment. Preparation includes planning implementation and inventorying proposed challenges. Implementation focuses on the process of assuring and balancing fidelity to the evidence-based program (EBP) delivered with adaptations needed to assure program success. Sustainment focuses on maintenance and program and factors impacting implementation over the long haul. The PCM is based on complexity theory and was empirically derived through a mixed method comparative assessment of high and low performing primary care practices that implemented an intervention to improve delivery of services [55–57].

The PCM complements EPIS in important ways differentiating motivation (energy for change) and capacity or resources for change (capability). In addition, it emphasizes the importance of interdependencies that manifest among the contextual factors influencing intervention effectiveness and is used to guide the intervention. Figure 1 shows the relationship between the conceptual models being used (EPIS and PCM) and their associated role in the study design.

**Fig. 1 Fig1:**
[figure not shown]
Conceptual model that blends the Exploration, Preparation, Implementation, and Sustainment (EPIS) framework and the Practice Change Model (PCM)

### Identifying actionable strategies: a multi-method stakeholder informed process

Early phases of this research were part of the Exploration and Preparation phases, while the current protocol describes the Implementation and Sustainment phases. The exploration and preparation phases used a combination of depth interviews and Delphi panels [58] to identify potential interventions. As part of the exploration phase, we executed a needs assessment through depth interviews with 40 national and local stakeholders representing patients/patient advocates, health care clinicians (separately primary care and oncology), policy influencers, and researchers to generate evidence from different perspectives on the role of primary care for patients with a history of breast cancer. Participants were recruited either via nomination by the grant advisory committee or through snowball sampling.

As part of the preparation phase, we used these findings to perform Delphi panels with 23 experts in care for patients with a history of breast cancer. Participants engaged in a 4-round online Delphi panel to identify strategies for defining and fostering primary care’s role in care for patients with a history of breast cancer. Innovators included primary care physicians, oncologists, researchers and policy influencers from government and professional organizations.

Guided by the insights from the exploration and preparation phases and PCM actionable evidence-based protocols for breast cancer survivorship care, we have created a list of actionable breast cancer follow-up strategies that will be implemented in a hybrid type 1 effectiveness-implementation cluster randomized study. The objectives of this intervention are to:Determine priority recommendations for patients with a history of breast cancer that are most compatible for adoption in primary care practices.Investigate the organizational and innovation adaptations needed to support the integration of priority recommendations for breast cancer follow-up care.Understand how physicians and staff perceive the utility and sustainability of the priority recommendations for breast cancer patients in day-to-day practice operations.

## Methods

### Participants and procedures

This study will be conducted in 26 practices recruited from 79 primary care practices in the Robert Wood Johnson (RWJ) Barnabas Health system [59]. RWJ Barnabas Health includes 207 primary care clinicians serving 73,000 patients throughout New Jersey. Practices will be randomized in pairs, by approximate size and type of practice, into 13 intervention or 13 waitlist control. The impact of this implementation will be measured using mixed methods to assess EPIS Implementation and Sustainment factors related to how organizational and contextual variables affect adoption, implementation and early sustainability for provision of follow-up care, symptom, and risk management activities at 6- and 12-months post implementation. The methods of this study have been reported using the SPIRIT guidelines (Additional file 1).

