### Patient-level outcome variables

The primary outcome variable will be breast cancer comprehensive follow-up care. This will be assessed by calculating the percentage of recommendations followed out of the total recommendations a given person is eligible to receive. Lower scores will indicate less comprehensive care. The number of recommendations may vary by patient depending on personal characteristics, like weight or smoking status. Research staff will collect data from the Electronic Health Record (EHR), conducting chart abstractions on 20 randomly selected patient records per practice at each time point. Measures of care coordination/management will be assessed from chart documentation of referral and/or treatment and screening for late and long-term effects, lifestyle, surveillance, and screening activities.

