#### Quantitative analysis

The primary outcome for each patient will be the percent of recommendations followed out of those for which the patient was eligible. Descriptive statistics and visualization techniques will summarize the practice averages of these percentages, overall and by treatment group and time. Additionally, we will calculate the practice rates of providing each individual service from patients for whom the service was appropriate and compare these across treatment arms and times. In formal analyses, hierarchical linear models we will study the effect of treatment on the primary outcome. Specifically, the model will include a random effect for practice to account for intra-practice correlation between patients, effects for time (baseline/follow-up) and intervention group (intervention/control), and patient characteristics such as age, race, count of co-morbidities. To test whether the intervention affects changes in the outcome over time, we will use an F-test of the interaction between treatment arm and time. In exploratory analyses, hierarchical logistic models will examine effects of the intervention on changes over time on rates of fulfillment of individual services.

Since practices in this study will be chosen for their diversity in patient population and management systems, analyses will also be conducted separately for each practice. These analyses will allow us to qualitatively examine characteristics of practices in which the intervention was effective versus those where it was not.

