##### Power calculations

For each individual patient, the percent of applicable recommendations that were followed will be calculated. Previous studies have seen rates between approximately 30% and 70% of individual recommendations being followed (e.g., colorectal cancer screening). Hence, we assume that the range for a vast majority of possible percentages lie between 20 and 80%, giving approximately a standard deviation of 15% (based on the Empirical Rule at with 95% of all observations falling within four standard deviations). Assuming this standard deviation, an interclass correlation of 0.1 [88], a dropout rate for practices of approximately 15%, and a mean difference in percentages between control and intervention practices of 15%, we would require 26 practices to achieve 90% power when conducting the test at the 0.05 level accounting for clustering within practice. If the interclass correlation was higher, say at 0.3, we would need to see a difference of 13% to achieve the same power with 26 practices.

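### Practices are randomised in pairs matched on size and type, but the stated primary model carries neither the pair nor the matching factors, so precision may be lost if those factors predict change over time

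*Protocol article*

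**What the plan says.** Under Participants and procedures the article restricts the allocation: "Practices will be randomized in pairs, by approximate size and type of practice, into 13 intervention or 13 waitlist control".

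Under Quantitative analysis it names the terms of the primary model. For clustering, "the model will include a random effect for practice to account for intra-practice correlation between patients". For fixed effects, "effects for time (baseline/follow-up) and intervention group (intervention/control), and patient characteristics such as age, race, count of co-morbidities". For the test, "we will use an F-test of the interaction between treatment arm and time".

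The list of covariates is open-ended, but only for patient characteristics. Pair, practice size and practice type do not appear. The Power calculations section allows for clustering within practice and for about 15% practice dropout, and does not mention matching.

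**The concern.** Size and type were chosen as matching factors, presumably because they were expected to matter for how practices deliver follow-up care. An analysis usually carries the factors that restricted the randomisation. If two practices in a pair tend to change alike, a comparison that ignores the pair does not use that likeness to reduce its error. Inference rests on 26 practices, or about 22 after the planned dropout, so any recoverable precision at practice level is worth having.

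The article does not leave the model open on this point. It lists the terms, and an analysis faithful to that list would leave the matching out.

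**Working it through.** **Inputs from the article.** 13 pairs; 20 records per practice per time point ("conducting chart abstractions on 20 randomly selected patient records per practice at each time point"); SD 15 points ("giving approximately a standard deviation of 15", in percent); ICC 0.1 ("an interclass correlation of 0.1"), with 0.3 as the sensitivity case; arm-by-time test. **Assumed, because the article is silent:** the within-pair correlation r of practice-level change, and the share of practice variance that varies over time.

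**1. Does any stated figure rest on matching?** The ICC 0.3 case reproduces as an unmatched follow-up comparison. The design effect is 1 + 19 × 0.3 = 6.7. With 11 practices per arm, SE = √(2 × 225 × 6.7/(20 × 11)) = 3.70, and the difference detectable with 90% power on 20 df is 12.6 points. So 13 points needs 22 practices, and 22/0.85 gives 26. The ICC 0.1 case does not reproduce: the same method gives a detectable difference of 8.3 points, not 15. That is a separate matter. Neither figure takes credit for matching.

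**2. What does a pair main effect do to the stated test?** With a practice intercept only, the variance of the interaction is (2/13) × 2σ²e/20.
- ICC 0.1: σ²e = 202.5, variance 3.115, SE 1.765.
- ICC 0.3: σ²e = 157.5, variance 2.423, SE 1.557.

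Adding pair as a main effect leaves both unchanged, because a stable pair level cancels out of a within-practice change. Matching helps only through pair (or size and type) by time.

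**3. What could be lost in an unpaired test of practice-level changes?** The ratio of paired to unpaired SE is √(1 − r).

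| r | √(1 − r) | Unpaired SE too large by | Level of nominal 5% test, 2[1 − Φ(1.96/√(1 − r))] |
|---|---|---|---|
| 0 | 1 | 0% | 5.0% |
| 0.2 | 0.894 | 12% | 2.8% |
| 0.3 | 0.837 | 20% | 1.9% |

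**4. What does full pairing cost?** Degrees of freedom fall from 24 to 12. (2.064/2.179)² = 0.897, so break-even is near r = 0.10. A power-based calculation gives 0.086 with 13 pairs and 0.105 with 11.

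A simulation on practice changes (13 pairs, half the practice variance time-varying) shows both sides:

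| ICC, true difference | Share of practice variance explained by pair | Power, unpaired | Power, paired |
|---|---|---|---|
| 0.1, 8 points | 0 | 0.849 | 0.816 |
| 0.1, 8 points | 0.3 | 0.870 | 0.877 |
| 0.1, 8 points | 0.5 | 0.879 | 0.914 |
| 0.3, 10 points | 0 | 0.769 | 0.733 |
| 0.3, 10 points | 0.3 | 0.798 | 0.843 |
| 0.3, 10 points | 0.5 | 0.813 | 0.911 |

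**5. Do the levels in step 3 describe the stated model?** No. Pair-correlated change requires practices to differ in their change, and the stated model has no term for that. Take ICC 0.1 with half the practice variance (11.25 of 22.5) time-varying.
- The variance of a practice's observed change is 2 × 11.25 + 2 × 202.5/20 = 42.75.
- At r = 0.25 the true SE is √((2/13) × 42.75 × 0.75) = 2.22.
- The intercept-only model pools the between-time variation into its residual: (24 × 427.5 + 988 × 202.5)/1012 = 207.8, where 427.5 = 202.5 + 20 × 11.25. Its SE is √((2/13) × 2 × 207.8/20) = 1.79.
- The ratio is 0.805, and 2[1 − Φ(1.96 × 0.805)] is about 11%.

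So in this setting the model as written rejects too often, not too rarely. The cause is the missing practice-by-time term, not the missing pair: at r = 0 the same arithmetic gives about 17%.

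**The case against.** The strongest reply is that matching may be used for balance alone. Omitting the pair does not bias the estimate and does not by itself inflate type I error. The interaction test removes stable size and type differences already. The documents do not show that size or type predicts change, and at low correlation a paired analysis is the weaker one. All of this stands, and it is why the loss can be called only possible.

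The assumed correlation of 0.2 to 0.3 is also demanding. In the setting of step 5, only 22.5/42.75 = 53% of the variance of observed change lies between practices. Approximate size and type would therefore have to explain 38% to 57% of the true variation in change.

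It can also be said that a condensed article leaves such detail to the analysis plan. That carries less weight here, because the model terms are listed and the list is open only for patient characteristics.

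A reader might go further and infer that the planned test is conservative, with intervals too wide by the amount that matching worked. Step 5 shows that this does not follow for the stated model. A reader might also shrink the 8.3-point detectable difference by √(1 − r). That would apply a correlation of change to a follow-up-only comparison and ignore the lost degrees of freedom, so no such range should be quoted.

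**Conclusion.** The mismatch is clear from the text: the randomisation is paired on size and type, and the named model terms contain neither. The consequence is a possible loss of precision, not an invalid comparison.

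Its size cannot be fixed from the documents. It is zero if size and type do not predict change. For an unpaired test of practice-level changes it reaches 12% to 20% of the SE at an assumed correlation of 0.2 to 0.3. The article supports no particular value, and no stated power figure depends on one.

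Confidence is high on the mismatch and moderate at most on its importance. The correction is worth making because it is cheap and is needed for the matching to contribute anything beyond balance. It must not be made without a practice-by-time term. If practices differ in their change, the model as written understates the SE whether or not matching terms are added.

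**What to change.** In the Quantitative analysis section, extend the primary model in three ways:
- Add practice size and practice type as fixed effects with their time interactions, or alternatively a random pair-by-time effect. A pair main effect alone achieves nothing.
- Add a random practice-by-time effect, so that the SE of the arm-by-time interaction is valid.
- State that a practice whose pair-mate drops out stays in the analysis. At 15% dropout about 4 of 26 practices leave. If losses are independent, about 13 × 0.85² = 9.4 pairs remain intact. The covariate and random-effect forms both allow the unpaired practices to be kept.

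Settle this before outcomes are compared by arm. The matching factors are already in hand from the randomisation. The cost is a few practice-level degrees of freedom: three, for example, would move the critical t from 2.064 (24 df) to 2.080 (21 df). Fully fixed pair effects cost 12 and are not advised unless a within-pair correlation above about 0.10 can be justified.
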